## 1. Clinical study title and phase

### 1.1 Title

Ability of nafamostat mesilate to prolong filter patency during continuous renal replacement therapy in patients with a high risk of bleeding

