#### 8.2.8 Filter life span

To check filter life span, every filters used during CRRT was checked for initiation time, discontinuation time, and the reason for filter failure.

The reason for filter failure is categorized as follows;

- ① Due to filter clot
- ② Ultrafiltrate loss is less than 150mL/hr in recent 3 hours
- ③ Persistent transmembrane pressure > 200mmHg
- ④ Vascular access abnormality
- ⑤ Extracorporeal circuit abnormality
- ⑥ Due to another apparatus (such as radiologic examination)
- ⑦ Etc.

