#### 11.1.1 Primary validity assessment variable

Mortality at ICU

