#### 11.1.2 Secondary validity assessment variables

- ① Mortality in hospital
- ② Mortality at 28 days after initiation of CRRT
- ③ CRRT duration
- ④ Hospitalization period in ICU
- ⑤ Hospitalization period
- ⑥ .Survival period
- ⑦ Filter life span
- ⑧ Blood loss
- ⑨ Transfusion

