#### 11.2.2 Secondary validity assessment variables

(1) Mortality in hospital

We will check whether the patients' mortality in hospital after CRRT is 50%, and additionally whether there is any statistical significant difference between two groups.

(2) Mortality at 28 days after initiation of CRRT

We will check whether the patients' mortality at 28 days after initiation of CRRT is 50%, and additionally whether there is any statistical significant difference between two groups.

(3) CRRT duration

We will check the duration of CRRT at ICU between the two groups.

(4) Hospitalization period in ICU

We will check the patients' duration within ICU until recovery to general ward or death.

(5) Hospitalization period

We will check the patients' duration within hospital until discharge or death.

(6) Survival period

We will calculate the survival 28 days after CRRT in both groups. Each patient's survival period is sought to calculate median survival time.

(7) Filter life span

We will check each filter life span during CRRT when CRRT is discontinued and calculate average filter life span.

(8) Blood loss

We will check blood loss at filter change during CRRT.

(9) Transfusion

We will check the amount of transfusion during CRRT.

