#### 11.3.3.2 Secondary validity assessment value

(1) Mortality within hospital

Mortality within hospital is presented.

(2) Mortality at 28 days after initiation of CRRT

Mortality at 28 days after initiation of CRRT is presented.

(3) CRRT duration

The mean, standard deviation, maximum, minimum values of CRRT duration in each group are presented.

(4) ICU hospitalization period

The mean, standard deviation, maximum, minimum values of ICU hospitalization period after ICU initiation in each group are presented.

(5) Hospitalization period

The mean, standard deviation, maximum, minimum values of hospitalization period after CRRT initiation in each group are presented.

(6) Survival

Survival rate at 28 days after initiation of CRRT is calculated using Kaplan-Meier analysis with data of all subjects in the clinical study including censored data. Also, Kaplan-Meier curve is presented as graph, and median survival time of each group is presented.

(7) Filter life span

The mean, standard deviation, maximum, minimum values of filter life span which is changed during the study in each patient are presented.

(8) Blood loss

The mean, standard deviation, maximum, minimum blood loss during each filter change in CRRT with each patient are presented.

(9) Transfusion

The mean, standard deviation, maximum, minimum values of transfusion during CRRT in each patient are presented.

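### Filter life span, the outcome named in the title, is fixed as a plain mean that ignores why each filter stopped and leaves the last filter's handling unclear

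*Protocol*

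**What the plan says.** The title in Protocol 1.1 is about the "Ability of nafamostat mesilate to prolong filter patency during continuous renal replacement therapy". The primary variable in 11.1.1 is "Mortality at ICU"; filter life span appears in the list of secondary variables in 11.1.2.

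Section 8.2.8 sets out the data: "every filters used during CRRT was checked for initiation time, discontinuation time, and the reason for filter failure". It then lists seven reasons, all under the label of filter failure. In paraphrase:

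- Reasons 1 to 3: clotting, low ultrafiltrate, persistently high transmembrane pressure.
- Reason 4: a vascular access problem.
- Reason 5: a problem in the extracorporeal circuit.
- Reason 6: removal because of other equipment, with imaging as the example.
- Reason 7: an open residual category.

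Section 11.2.2 (7) looks at each filter's life when CRRT is discontinued and will "calculate average filter life span". Section 11.3.3.2 (7) then specifies: "The mean, standard deviation, maximum, minimum values of filter life span which is changed during the study in each patient are presented". One item earlier, 11.3.3.2 (6) specifies Kaplan-Meier estimation, with censored observations included, for patient survival.

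**The concern.** Time to filter clotting is a time-to-event quantity with several ways of stopping, and only some of them bear on anticoagulation. A filter removed in working order for a scan or an access problem shows only that it had not clotted by then. Averaging its run time with those of clotted filters treats it as having reached the end of its life, which pulls the two arms together.

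The last filter raises a second problem. Sections 8.2.8 and 11.2.2 (7) suggest that the filter running when CRRT ends, or when the patient dies, enters at its run time. The wording of 11.3.3.2 (7), which qualifies filters as those changed, can be read as covering exchanged filters only. The two readings give different datasets, and neither suits a patency question.

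At stake is the answer to the question in the title: a real effect on clotting could be diluted, or the result could depend on which reading is chosen after the data are in.

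**Working it through.** **The plan's own figures.** The protocol gives no assumed filter life, filter effect or share of non-clot stops. Its one calculation, in 6.3.2, reproduces: 1.645² × 0.5 × 0.5 / 0.15² = 30.06, rounded up to 31 per group; 31 / 0.95 = 32.6, rounded up to 33. It is a precision calculation for one mortality proportion and says nothing about filters.

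**Dilution of the clotting effect (all inputs assumed).** Let clotting and non-clot stops be independent and exponential, with the same non-clot rate in both arms. Let s be the share of control filters that stop for non-clot reasons and HR the clotting hazard ratio, nafamostat against control. The crude mean run time is 1 / (clotting rate + non-clot rate). Dividing the two arms' means gives

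ratio of crude means = 1 / (s + (1 − s) × HR),

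whereas the true ratio of mean times to clotting is 1 / HR.

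| s (control) | HR 0.5 (true ratio 2.0) | HR 0.667 (true ratio 1.5) |
|---|---|---|
| 20% | 1 / (0.2 + 0.4) = 1.67 | 1.36 |
| 40% | 1 / (0.4 + 0.3) = 1.43 | 1.25 |
| 60% | 1 / (0.6 + 0.2) = 1.25 | 1.15 |

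With HR 0.5, the non-clot shares in the nafamostat arm are 33%, 57% and 75%. The same result in hours for the middle row: mean time to clotting 20 h against 40 h and non-clot stops at mean 30 h give 1 / (1/20 + 1/30) = 12.0 h and 1 / (1/40 + 1/30) = 17.1 h, ratio 1.43.

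**Information lost.** A simulation on the same model (HR 0.5, 31 filters per arm, one per patient, two-sided 5%, 3,000 runs) compared a Welch t-test on crude run times with a log-rank test censoring non-clot stops. Power was 48%, 27% and 11% for the first and 63%, 50% and 31% for the second, for s = 20%, 40% and 60%. The protocol names no test for filter life span, so this shows relative information and not the trial's operating characteristics.

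**The last filter.**

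- Reading A (8.2.8 with 11.2.2 (7)): every filter counts, including the one in use when CRRT ends. A run cut short by the end of CRRT or by death enters as a complete life, although it is only a lower bound on time to clotting.
- Reading B (11.3.3.2 (7), exchanged filters only): the last filter is left out. A patient whose single filter lasted throughout CRRT contributes nothing. If nafamostat works, more such patients would be expected in that arm, so its best results would be the ones removed.

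**Several filters per patient.** The wording of 11.3.3.2 (7) does not settle whether a patient's filters are first averaged or are pooled across patients.

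**The case against.** The strongest reply is that filter life span is a descriptive secondary outcome and that all-cause filter life is a legitimate quantity. It is what the bedside team experiences, and in an open-label trial (4.3) it does not depend on an unblinded judgement of why a filter stopped. The drop from 2.0 to 1.43 then partly reflects a different estimand, and every input to it is assumed. The stop reasons are recorded, and nothing forbids their use. All of this stands. It is the reason to keep the all-cause mean alongside the new analysis and not to treat the point as critical. It does not remove the gap: the protocol itself fixes the summary in two places, so this is not a detail left to a SAP, and that summary does not isolate patency.

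A reader might infer more than the text supports in four ways.

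- **That death and end of CRRT are counted as filter failure.** No section says so. Neither is among the seven reasons; only the residual category could hold them, and 11.3.3.2 (7) can be read the opposite way.
- **That false-positive rates are inflated by pooling filters.** No test is specified for this outcome, and the wording about each patient may mean patient-level summaries.
- **That this is the weakest method in the plan.** The same descriptive summary is used for CRRT duration, lengths of stay, blood loss and transfusion.
- **That filter patency must become the primary endpoint.** The title does differ from 11.1.1, but sections 3, 6.3.2, 7.1 and 11 consistently make mortality the objective. The position of filter life span in the secondary list implies no ranking.

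**Conclusion.** The concern holds in this form: the outcome named in the title is fixed as an uncensored mean that takes no account of stop reason, although the reason is recorded for every filter and a censoring method is already specified for survival. The treatment of the last filter is undefined and inconsistent between sections. Under exponential times with equal non-clot rates in the two arms, a true two-fold gain in time to clotting would show as a ratio of 1.25 to 1.67 when 60% to 20% of control filters stop for non-clot reasons. The direction follows from that model; the size cannot be taken from the documents. It should be fixed, but it does not undermine the trial's stated primary objective.

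**What to change.** Rewrite 11.2.2 (7) and 11.3.3.2 (7) to match:

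- Include every filter, the last one among them.
- Define the event as stopping for reasons 1 to 3 of 8.2.8. Censor at reasons 4, 6 and 7, at end of CRRT and at death.
- Describe this as a cause-specific analysis, since death and the other stops are competing events and censoring them does not give the all-cause probability of losing a filter.
- Censor reason 5 in the main analysis and count it as an event in a sensitivity analysis, because a circuit abnormality could include clotting in the circuit.
- Compare arms by Kaplan-Meier and a Cox model with patient-clustered standard errors, stratified by diabetes, the randomisation stratum in 7.5. Report the first filter per patient as supportive.
- Keep the all-cause mean, SD and range as a descriptive summary and as a check on open-label attribution of stop reasons.

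The cost is wording and a little more analysis work. Start time, stop time and reason are already collected; death or end of CRRT has to be linked to the last filter from records the trial already keeps. The primary endpoint and sample size are unaffected.

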##### 3.1.2 Secondary end point

We compared CRRT duration, ICU, hospitalization duration, survival, filter life span, blood loss, and transfusion between two groups and efficiency and safety of nafamostat mesilate.

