#### 8.2.16 Blood loss

After initiation of CRRT, amount of blood loss at filter exchange was examined.

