#### 8.3.2 Medication phase (randomization and after initiation of CRRT)

- ① After screening, change in medication history is checked.
- ② Every examination including clinicopathologic test and assessment is collected to finally evaluate the patient's suitability as a subject.
- ③ Patient is given a randomization number by random enrollment.
- ④ Study medication is administered.
- ⑤ Hematologic examination was conducted every 72 hours after initiation of CRRT.
- ⑥ Vital sign (blood pressure, body temperature, pulse rate, respiratory rate) is assessed every 4 hours after initiation of CRRT.
- ⑦ Filter life span and reason for discontinuation is sought.
- ⑧ Blood loss is checked at filter change after initiation of CRRT.
- ⑨ Transfusion (packed RBC, free frozen plasma, platelet concentrate) is assessed after initiation of CRRT.
- ⑩ Any changes in medication are recorded.
- ⑪ Adverse event is investigated.
- ⑫ Bleeding accident is checked.

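### Blood loss is summarised per filter change, which divides out the number of changes and can hide a fall in loss per patient

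*Protocol*

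**What the plan says.** Section 3.1.2 lists blood loss among the secondary comparisons: "filter life span, blood loss, and transfusion between two groups". Every section that says how it is obtained ties it to the filter exchange:

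- Section 8.2.16: "After initiation of CRRT, amount of blood loss at filter exchange was examined".
- Section 8.3.2: "Blood loss is checked at filter change after initiation of CRRT".
- Section 11.2.2 (8): "We will check blood loss at filter change during CRRT".

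Section 11.3.3.2 (8) then fixes the statistic: "The mean, standard deviation, maximum, minimum blood loss during each filter change in CRRT with each patient are presented". No section defines a total per patient or a loss per unit of CRRT time. The neighbouring item, transfusion, is set up in 11.2.2 (9) as a quantity over the whole course: "We will check the amount of transfusion during CRRT".

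The expected effect on the circuit is in the title (1.1): "Ability of nafamostat mesilate to prolong filter patency during continuous renal replacement therapy in patients with a high risk of bleeding". Section 8.2.8 records start time, stop time and reason for failure for every filter. The schedule (Study schedule and 8.1) marks blood loss at closing as well as during treatment, but the closing procedures in 8.3.3 do not list it, and neither 8.2.16 nor 11.3.3.2 (8) says what the closing entry records or how it is used.

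**The concern.** A patient's circuit blood loss is the number of losses times the size of each. Longer filter life acts on the number. The chosen summary keeps only the size. If the drug works by making exchanges rarer and leaves the loss at each one much the same, the two arms look alike on this endpoint although futhan patients lose less blood. In a population selected for bleeding risk, the loss a patient bears over the course is the quantity of interest, and the comparison promised in 3.1.2 would not show it.

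There is a second, smaller problem. A patient whose first filter lasts the whole CRRT course has no filter change and therefore no value. That patient leaves the summary instead of counting as a low or zero loss.

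**Working it through.** **The plan's own figure.** The protocol gives no numerical assumption for blood loss or filter life. Its only calculation is the sample size for mortality in 6.3.2, which reproduces: 1.645² × 0.5 × 0.5 / 0.15² = 30.06, rounded up to 31; 31/0.95 = 32.6, rounded up to 33. It does not bear on this point. All inputs below except the 31 patients per arm are assumptions.

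**Notation.** T is hours of CRRT, F is filter life in hours, and v is blood lost per circuit end. Circuits used = T/F. Exchanges = T/F − 1 when the last filter ends with CRRT.

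**General form, counting all circuit ends.**

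- Loss per 24 h of CRRT = 24v/F.
- Ratio of loss rates, futhan to control = (v_fut/v_con) × (F_con/F_fut).
- Ratio of per-change means = v_fut/v_con.

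The per-change mean drops the second factor, F_con/F_fut, which is the one that patency changes.

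**Worked example.** T = 72 h, the same v in both arms, control filter life 12 h.

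| Filter life, control v futhan | Circuit ends | Change in total | Exchanges only | Change in total | Per-change difference |
|---|---|---|---|---|---|
| 12 h v 24 h | 6 v 3 | −50% | 5 v 2 | −60% | 0% |
| 12 h v 18 h | 6 v 4 | −33% | 5 v 3 | −40% | 0% |

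The two counts differ only in whether the last filter's loss is included. The conclusion is the same under either.

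**Other inputs.** With control filter life 16 h and futhan 20, 24 or 32 h, the ratio of loss per CRRT day is 16/20 = 0.80, 16/24 = 0.67 or 16/32 = 0.50. The per-change ratio is 1.00 each time. For v = 150 mL and 16 h against 24 h, this is 225 against 150 mL per CRRT day and 150 against 150 mL per change. The ratios depend neither on v nor on T.

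**Simulation.** Assumptions: 31 patients per arm, 96 h of CRRT, exponential filter life with mean 16 h against 24 h, loss per exchange 150 mL (SD 50) in both arms, two-sided test at 0.05. The share of trials that reject was:

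- all changes pooled: 4.6%;
- each patient's mean over changes: 4.7%;
- loss per CRRT day: 91%.

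The first two are the nominal error rate. Reading the words about each patient in 11.3.3.2 (8) as a within-patient mean therefore does not help, because the denominator is still the number of changes.

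**Patients without an exchange.** With 24 h of CRRT or less and a 24 h filter life, exchanges = 24/24 − 1 = 0, so there is no per-change value. With equal v, removing such patients leaves v against v, which is still a 0% difference.

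**The case against.** Four objections have force.

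1. **The 0% rests on equal loss per change.** Section 8.2.8 lists several reasons for filter failure, from clotting to access problems to interruption for another procedure. If loss differs by reason and the drug changes the mix of reasons, the per-change mean could move. This stands. A reader might infer that a drug which halves circuit loss must show nothing on this endpoint. That follows only under the equal-loss assumption, which the protocol neither makes nor contradicts.

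2. **Recording at exchange is not a defect.** A reader might blame the measurement itself. But values taken at each exchange can be summed per patient, and the sum does reflect fewer exchanges. The fault is confined to the summary in 11.3.3.2 (8). What the closing entry means is a matter for clarification.

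3. **The benefit is visible elsewhere.** Filter life span is a separate secondary variable, and transfusion is measured over the whole of CRRT. It would be wrong to say that the trial cannot show longer patency. Filter life span is still not a volume of blood, so it does not answer the blood loss comparison. That the benefit comes through fewer exchanges is an inference from the title; the protocol does not say so.

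4. **Loose wording and an unseen SAP.** Section 11.2.2 (8) names no denominator, and aggregation within a patient could be settled in an SAP. But 11.3.3.2 (8) does name the unit, and loss at each filter change is its natural reading.

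A reader might also infer that losing patients without an exchange tilts the comparison against the arm with longer filter life. The documents do not support this: under equal loss the result is null, not reversed, and no figure is given that would show a shift.

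**Conclusion.** The point holds for the summary statistic. As written, the endpoint describes the size of the loss at a change and says nothing about how often changes occur. If loss per change is similar in both arms, an effect that works through fewer exchanges yields a difference of about 0%, while loss per patient falls by 33% to 60% in the 72 h examples, depending on the filter lives assumed and on whether the last filter counts. Leaving out patients without an exchange loses information, with no demonstrated direction of bias.

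The reach is limited. This is one of nine secondary variables in a trial whose primary endpoint is ICU mortality. Longer patency would still show under filter life span, and an exchange-based rate can be derived from what is already recorded. It should be corrected because the better summary costs little.

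**What to change.** - **Sections 11.2.2 (8) and 11.3.3.2 (8):** define blood loss as each patient's total recorded circuit loss divided by that patient's CRRT time, in mL per 24 h of CRRT. Enter zero for a patient with no exchange and no recorded loss. Compare this between the arms and keep the per-change mean, SD, maximum and minimum as descriptive. A rate is safer than a raw total, because the total also depends on how long CRRT lasts and on death. Show the total and the CRRT hours beside it.
- **Section 8.2.16:** state that the closing blood loss entry already in the schedule records the loss at the last filter and counts in the total. List it in 8.3.3 as well.

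The cost is a few sentences of protocol text, one clarified data item at closing and a little more analysis. Filter start and stop times are already collected. Recording the last filter's loss is a small clarification of data collection, not wording alone. If that value cannot be obtained, the exchange-only total per 24 h still reflects the number of changes.

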#### 11.3.4 Safety data

##### 11.3.4.1 Adverse event

All adverse events that have been reported during the study will be charted, and incidence of adverse event will be calculated.

##### 11.3.4.2 Clinicopathologic examination result

All laboratory result is presented and compared with the result from screening.

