## ■ Study Protocol Summary

|                     |                                                                                                                                                                                                                                                                                                                                                                                                                                                                                                                                                                                                                                                                                                                              |
|---------------------|------------------------------------------------------------------------------------------------------------------------------------------------------------------------------------------------------------------------------------------------------------------------------------------------------------------------------------------------------------------------------------------------------------------------------------------------------------------------------------------------------------------------------------------------------------------------------------------------------------------------------------------------------------------------------------------------------------------------------|
| Method              | 
This study is a single-center, randomized, open clinical study to evaluate mortality, patients' recovery rate, safety between nafamostat mesilate group and no-anticoagulation group in patients who are prohibited from using heparin.
 
When the ICU patient who has hemorrhagic tendency and in need of CRRT voluntarily agrees to participate in the clinical study, the patients who are suitable by inclusion criteria are randomly assigned to each group. Nafamostat mesilate will be administered until CRRT is ceased due to various reasons, and after which patients mortality within 28 days after CRRT initiation and renal functional recovery at 1st outpatient department follow up.
 |

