| Validity assessment | 
 
· primary end point: mortality within ICU
 
· secondary end point               
 
① In-hospital mortality
 
② Mortality within 28 days after initiation of CRRT
 
③ CRRT duration
 
④ ICU hospitalization period
 
⑤ Total hospitalization period
 
⑥ Survival
 
⑦ Filter life span
 
⑧ Blood loss
 
⑨ transfusion
 
 
 
                                                                                                                                                                                                                                         |
| Safety assessment   | Adverse events, clinical pathology examination (hematologic, blood coagulation test, lipid exam, urine analysis)                                                                                                                                                                                                                                                                                                                                                                                                                                                                                                                                                                                                             |

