## 7. Clinical study method

## 7.1 Clinical study design

This study is single center, randomized, open clinical study to compare mortality, patients' recovery, safety using nafamostat mesilate and no-anticoagulation during CRRT in ICU patients who has hemorrhagic tendency that prohibits usage of heparin.

When ICU patients with hemorrhagic tendency that needs CRRT who fits inclusion/exclusion criteria voluntarily agrees to participate in the study, patients who fit the inclusion criteria by subject compatibility result are randomly assigned to each group. Since CRRT duration can be different due to patient's condition, nafamostat mesilate administration will be continued until CRRT is discontinued. Afterwards, mortality after 28 days of CRRT discontinuation and renal recovery at 1st outpatient department visit will be compared between each group.

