###### ② Hyperkalemia

(Pancreatitis: 0.19%, DIC: 4.53%, anticoagulation for extracorporeal circuit: 0.02%; Re-examination conclusion report result in Japan)

Extra caution is required due to possibility of hyperkalemia, when using potassium sparing diuretics, potassium containing medication. When it occurs, immediate

discontinuation of the medication and proper management should follow. Also, there have been some cases of arrhythmia due to hyperkalemia.

(5) Other adverse events

- ① Skin: Occasionally rash, rarely erythema, urticaria occurred, and the medication is discontinued after the symptom appears.
- ② Musculoskeletal: Myalgia and arthralgia have been reported.
- ③ Gastrointestinal: Anorexia, diarrhea, nausea, vomiting have been reported.
- ④ Hepatobiliary: Occasionally GOT/GPT elevation, ALP elevation, LDH elevation, total bilirubin elevation and Jaundice have occurred.
- ⑤ Hematologic: Occasionally leucopenia, eosinophilia, thrombocytopenia, and thrombocytosis have occurred. Bleeding tendency can occur, and in this occasion, medication dose will be tapered or discontinued.
- ⑥ Cardiovascular: Palpitation, hypertension and hypotension can occurred.
- ⑦ Urologic: Intermittently BUN/Creatinine elevation occurred.
- ⑧ Systemic: Headache, chest pain, general weakness, chest discomfort, and rarely fever have been reported.
- ⑨ Administration site: Rarely pain and angiitis with swelling occurred.

4. General precaution

- (1) Hyperkalemia and hyponatremia due to potassium excretion inhibition and sodium excretion acceleration can be occurred. Hence serum potassium and sodium level should be checked regularly and if any abnormalities have been observed, immediate discontinuation and proper management should be performed.
- (2) When using Potassium containing medication and potassium sparing diuretics in combination, be cautious about hyperkalemia. Also, when abnormal serum potassium level is confirmed, electrocardiography should be checked to identify arrhythmia. When used in extracorporeal circuit, this medication can aggravate hemorrhage. Hence close observation is required, and if needed, the medication should be tapered or discontinued

5. Administration to elderly

Elderly are generally with reduced physiologic function and careful caution for dose reduction is required.

6. Administration to pregnant or lactating female

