## 11. Efficacy assessment criteria, assessment method, and analysis method (Data analysis method)

### 11.1 Assessment criteria

Primary and secondary validity assessment variable is as follows and each assessment variables are analyzed with classification of futhan and no-anticoagulation group.

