### 11.3 Analysis method

#### 11.3.1 General principal of result analysis

The data retrieved from the patients during the study is analyzed by Safety analysis, ITT (Intent-To-Treat) analysis and PP (Per Protocol) analysis.

The Safety analysis is analysis including all data from patients in futhan group who have taken the medication at least once and no-anticoagulation group

The ITT analysis is analysis including all data from patients who have been confirmed whether he or she is dead or alive in futhan group who have taken the medication at least once and no-anticoagulation group. And when there is a missing value or patient drop out before the study is over, the latest value can be analyzed as data acquired at relevant time (Last Observation Carried Forward Method).

The PP analysis is analysis including the data from patients who have successfully concluded the study protocol.

The data regarding validity is principally analyzed by PP analysis, and additionally analyzed by ITT analysis.

The data regarding safety is principally analyzed by Safety analysis.

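### Section 11.3.4.2 compares laboratory results only with screening, although the protocol sets out a between-group comparison of safety

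*Protocol*

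**What the plan says.** Section 11.3.4.2 of the protocol is one sentence: "All laboratory result is presented and compared with the result from screening". It names one comparator, the patient's own screening value.

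Other parts of the protocol set a different aim:

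- Section 7.1 describes a "randomized, open clinical study to compare mortality, patients' recovery, safety using nafamostat mesilate and no-anticoagulation during CRRT".
- The Method row of the Study Protocol Summary likewise speaks of evaluating "safety between nafamostat mesilate group and no-anticoagulation group in patients who are prohibited from using heparin". The End Point row lists a comparison of efficacy and safety between the two methods.
- The Safety assessment row of the summary lists clinical pathology beside adverse events. Its bracket does not name biochemistry, but section 8.2.5 includes potassium and sodium among the scheduled tests, and section 11.3.4.2 covers all laboratory results.
- Section 11.3.1 defines the safety population from both arms: "The Safety analysis is analysis including all data from patients in futhan group who have taken the medication at least once and no-anticoagulation group".

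The one general rule on analysis by group is in section 11.1, and it is written for efficacy: "Primary and secondary validity assessment variable is as follows and each assessment variables are analyzed with classification of futhan and no-anticoagulation group". No counterpart is given for safety variables.

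**The concern.** The design promises a randomised safety comparison, and the stated laboratory analysis is before-and-after. A change from screening holds any drug effect plus whatever would have happened to the patient anyway. Two sources of shared change follow from the protocol itself.

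- **CRRT.** Screening comes before CRRT in everyone. Later tests are taken every 72 hours during CRRT or when it stops (section 8.2.5). Section 3.2 credits CRRT with correcting metabolic acidosis, so blood chemistry is expected to move in both arms.
- **Selection on a laboratory value.** Section 6.1 admits patients on platelets below 100,000, aPTT above 60 sec or PT-INR above 2.0, and section 8.2.5 uses the screening tests to confirm eligibility. Patients admitted on one of these values tend to drift back towards normal whatever the treatment.

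The tests of most interest are exposed to this. Section 9.1 warns of potassium and sodium disturbance ("Hyperkalemia and hyponatremia due to potassium excretion inhibition and sodium excretion acceleration can be occurred") and of aggravated haemorrhage in extracorporeal use. A fall in potassium from CRRT can offset a rise from the drug, and drift of aPTT or INR towards normal can offset systemic anticoagulation. Equally, an improvement seen in both arms could look like a benefit of nafamostat. The concurrent control arm is there to resolve this, and the stated comparison does not call on it.

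**Working it through.** **Plan's own figure.** Section 11.3.4.2 gives no number. The only calculated design figure is the sample size in section 6.3.2: 1.645² × 0.5 × 0.5 / 0.15² = 30.06, rounded up to 31 per group; 31 / 0.95 = 32.6, rounded up to 33. It reproduces. Only the 31 is used below.

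**Assumptions.** The protocol states no laboratory SD, no correlation between repeat values, no expected shift, and no test or significance level for laboratory data. The following are therefore assumed: one post-screening value per patient, correlation ρ = 0.5 with screening, two-sided 0.05, and t-tests. At ρ = 0.5 the SD of the change is √(2(1 − 0.5)) = 1, so shifts can be read directly in SD units.

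**1. Shared shift, no drug effect.** Let c be the shift that CRRT produces in both arms.

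- Within-arm paired t-test: noncentrality c√31. For c = 0.5 this is 2.78 against a critical value of 2.04 (30 df), which gives rejection in 77% of trials.
- Between-arm t-test of change: c cancels, so the noncentrality is 0 and rejection is 5%.

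| Shared shift (SD) | Within-arm significant | Between-arm significant |
|---|---|---|
| 0.25 | 27% | about 5% |
| 0.50 | 77% | about 5% |
| 0.75 | 98% | about 5% |
| 1.00 | 100% | about 5% |

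Simulation of 20,000 trials gave the same values.

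**2. Drug effect of 0.5 SD opposed by an equal shared shift.** The net change in the nafamostat arm is 0, so the within-arm test rejects in 5% of trials counting both directions, or about 2% in the harmful direction. The between-arm noncentrality is 0.5 / √(2/31) = 1.97, which gives about 49%.

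**3. Regression to the mean alone.** If patients enter because the value lies beyond a cut-off that a share q of the source population passes, the expected drift is (1 − ρ) × φ(z) / q, where z is the q-quantile of the standard normal. With q = 0.5 and ρ = 0.7 this is 0.3 × 0.399 / 0.5 = 0.24 SD. Over q = 0.3 to 0.7 and ρ = 0.5 to 0.9 it runs from 0.05 to 0.58 SD. If all 31 patients in the arm had been selected on that one value, the within-arm test would be significant in 9% to 93% of trials with no drug effect, and the between-arm test in 4.5% to 5.6%. That is an upper case, because not all patients qualify on the same test.

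**The case against.** The strongest reply is that section 11.3.4.2 fixes very little. It specifies no test, does not restrict itself to one arm, and does not say how a change is to be interpreted. A reader might infer that the protocol will count changes common to both arms as drug effects. The documents do not support that: no section says a change from screening will be attributed to nafamostat, and the Safety set includes the control arm. That stronger reading should not be held against the plan.

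Other parts of the reply also have weight:

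- Attribution is handled patient by patient elsewhere. Section 8.2.13 follows each abnormal result and evaluates its likely cause, section 12.4 grades causality against other explanations, and section 12.2 separates findings already present at screening. Comparison with screening serves that purpose. It does not give a group-level estimate of what the drug adds.
- Regression to the mean concerns three tests, and only patients who qualified on them. One of seven entry criteria is enough, and four are not laboratory cut-offs.
- Section 9.1 reports hyperkalemia in 0.02% for extracorporeal use against 4.53% for DIC, and section 3.2 describes the anticoagulant effect as limited to the circuit. Nothing in the protocol supports a 0.5 SD drug effect. DIC patients are eligible, however, so a potassium effect is not excluded.
- The calculations take one complete value per patient. The protocol allows the last result before death to stand in (section 8.2.5) and gives plasma and platelets as needed (section 8.2.17), so the 49% is idealised.
- The details of a laboratory contrast usually belong in the SAP, which is not at hand. That would excuse silence. Here the protocol does name a comparator, and it is not the one its stated aim requires.

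**Conclusion.** The point holds as a mismatch between aim and analysis. The protocol announces a between-group comparison of safety that includes laboratory data and defines a safety population from both arms. It then states, for laboratory data, only a comparison with screening. Followed as written, that comparison cannot separate a drug effect from change common to both arms.

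The figures of 77% against 5% illustrate the mechanism. They rest on an assumed shared shift of 0.5 SD, a correlation of 0.5, 31 patients per arm and a paired t-test at 0.05, none of which except the 31 comes from the protocol. They are not a forecast for this trial and not an error rate of a test that the protocol prescribes. The mismatch itself depends on none of them. The correction is worth making because it is cheap and bears on the safety question the trial sets itself; the primary endpoint is unaffected.

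**What to change.** Reword section 11.3.4.2 along these lines:

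> Laboratory results are presented by randomised group at screening and at each later scheduled time. At least for potassium, sodium, platelets, aPTT and PT-INR, the change from screening is compared between the futhan and no-anticoagulation groups as a difference adjusted for the screening value, with a confidence interval. Change from screening within a group is descriptive only.

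Model details can go to the SAP. Both arms already have these tests on the same schedule, so no patients, samples or visits are added. The cost is one paragraph, a little extra analysis, and intervals wider than those for within-arm change. With 31 per arm the between-group estimates will be imprecise, and the report should show that imprecision.
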